# PROTOCOL SYNOPSIS

| **Full Title** | Maintenance ElectroConvulsive Therapy in clozapine RESISTant schizophrenia |
| --- | --- |
| **Study Code** | MECT-RESIST |
| **Rationale** | Schizophrenia is one of the most severe and costly mental disorders in terms of human suffering and societal expenditure. About 15-30% of patients do not respond to all known antipsychotics, including clozapine, the current gold-standard in these cases. Electroconvulsive therapy (ECT) is well known to be highly effective in clozapine-treatment-resistant schizophrenia (CRS), and synergistic effects of clozapine and ECT have been demonstrated. However, relapse rates after successful courses of ECT are still very high, and evidence for maintenance ECT (mECT) in CRS is scarce at best. In our multi-center trial, we aim to examine the effectiveness of mECT in treatment-resistant patients with schizophrenia who improved after a course of routine ECT.  The scientific aim of the study is to test the hypothesis that maintenance ECT (mECT) plus treatment as usual (TAU) (intervention group) is superior to TAU alone (control group) for relapse prevention in CRS. The effectiveness of mECT will be examined by comparing time to relapse in the intervention group with the control group expecting a longer time to relapse in the intervention group. Secondarily, a lower number of patients with relapse is expected in the intervention group compared to the control group. Further secondary objectives are to test the hypotheses that the global level of functioning and quality of life will increase, and that depression, overall symptoms of the schizophrenic syndrome, concomitant catatonic symptoms, stress and self-stigmatization will decrease compared to the control group. It is also hypothesized that cognitive performance will improve over the course of the mECT. |
| **Primary Objective and Endpoint** | To compare after a successful series of routine electroconvulsive therapy (ECT) the overall effectiveness (time to relapse) of maintenance ECT (mECT) plus treatment as usual (TAU) versus TAU only.  Endpoint: Time to relapse (relapse defined as Brief Psychiatric Rating Scale (BPRS) ≥20% higher than individual BPRS at start of phase II at any following study visit OR any unscheduled readmission due to a worsening of psychiatric symptoms OR any unscheduled visit with an BPRS ≥20% higher than individual BPRS at start of phase II). The BPRS is evaluated by an unblinded rater at site and a blinded central rater. Readmission is decided by unblinded non-study related staff. The first relapse decision is used for analysis. |
| **Main Secondary Objectives and Endpoints** | 1. To compare side effect profile and safety between mECT plus TAU and TAU only 2. To compare psychopathological changes: mECT plus TAU versus TAU only   Endpoints:  - Number of relapse free subjects at the end of phase II  - BPRS at the end of phase II  - GAF, PANSS, HAMD, NCRS-dv, Q-LES-Q-18, SSMIS-SF, stigma-stress-scale at the end of phase II  - BPRS, GAF, PANSS, HAMD, NCRS-dv, Q-LES-Q-18,  SSMIS-SF, stigma-stress-scale at the end of follow-up  Assessment of safety:  Cognitive side effects profile (MMSE, THINC-integrated tool [THINC-it])  and safety. |
| **Study Design** | This is a multi-center, observer-blind, randomized, and actively controlled parallel-group clinical trial. |
| **Sample Size** | To be assessed for eligibility (n = 300)  To be allocated to trial (n = 140 in phase I)  To be analyzed (n = 84 randomized in phase II) |
| **Study Population** | Subjects (aged 18-65 years) with current diagnosis of schizophrenia according to Diagnostic and Statistical Manual of Mental Disorders, Fifth Edition (DSM-5), BPRS total score > 45 and history of clozapine resistant schizophrenia (CRS), which will include treatment-resistant schizophrenia with clozapine intolerance or absolute contraindications for clozapine. |
| **Interventions** | Experimental intervention:  All included subjects will be on a stable antipsychotic drug regime for 2 weeks before inclusion. All subjects will enter phase I and will receive a full course of routine ECT while being on stable antipsychotic medication. All ECT-responders (subjects with improvement of 30% or more on BPRS will enter phase II and will be randomly assigned to the experimental intervention (mECT plus TAU) or the control intervention (TAU) which both last 28 weeks. Non-responders (subjects without improvement of at least 30 % on BPRS scale) will not enter phase II.  Control intervention:  Subjects randomized to TAU only will continue on a stable drug regime for the next 28 weeks, but will not receive mECT. The number of clinical and study visits will be identical in both arms.  Intervention per patient:  Max. 35 weeks in total including a 1-week stabilization period, max. 6  weeks of routine ECT (maximal 18 sessions), and an active intervention  period of 28 weeks (15 ECT sessions).  Follow-up period: 12 months with or without maintenance ECT as determined by patients  Experimental and / or control off label or on label in Germany:  Both are on label in Germany |
| **Number of Sites** | 14 |

# SCHEDULE OF ASSESSMENT

| **Phase (duration)** | **0** | **I** | | **II** | | | | | | **Follow-Up** | | **Unscheduled**  **Visit** |
| --- | --- | --- | --- | --- | --- | --- | --- | --- | --- | --- | --- | --- |
|  | max. 1 week | Initial ECT series  (max. 6 weeks and max. 18 ECTs are allowed) | | 28 weeks | | | | | | 12 months | |  |
| **Visit** | **Screening/ inclusion** | **1** | **2** | **2a** | **2b** | **2c** | **2d** | **2e** | **3** | **4a** | **4b** |  |
| **Time** | Before start of stabilization*  (max. 7 days before visit 1) | 1-2 day(s) before the first ECT | 1 day after last ECT (week 0) | 3rd calendar week ** or  on the day of the 3rd mECT | 6^th^ calendar week after V2 or  on the day of the 6th mECT | 10^th^ calendar week after V2 or on the day of the 8th mECT | 14^th^ calendar week after V2 or on the day of the 10th mECT | 19^th^ calendar week after V2 or on the day of the 12th mECT | 28^th^ calendar week after V2  or on the day of the last mECT | 6 mo. after visit 3 | 12 mo. after visit 3 |  |
| Informed Consent | **x** |  |  |  |  |  |  |  |  |  |  |  |
| In-/Exclusion Criteria | **x** |  |  |  |  |  |  |  |  |  |  |  |
| Sociodemographics^1^ |  | **x** |  |  |  |  |  |  |  |  |  |  |
| Medical History |  | **x** |  |  |  |  |  |  |  |  |  |  |
| Concomitant Medication / Therapy |  | **x** | **x** | **x** | **x** | **x** | **x** | **x** | **x** | **x** | **x** | **x** |
| Vital Signs^2^ |  | **x** |  |  |  |  |  |  | **x** |  | **x** | **x** |
| Randomization^3^ |  |  | **x** |  |  |  |  |  |  |  |  |  |
| Adverse events |  |  |  | **x** | **x** | **x** | **x** | **x** | **x** | **x** | **x** | **x** |
| **Intervention** |  |  |  |  |  |  |  |  |  |  |  |  |
| TAU or mECT + TAU |  |  |  | **x**^4^ | **x**^4^ | **x**^4^ | **x**^4^ | **x**^4^ | **x**^4^ | **x**^5^ | **x**^5^ |  |
| **Questionnaires/tests** |  |  |  |  |  |  |  |  |  |  |  |  |
| Brief Psychiatric Rating Scale |  | **x** | **x** | **x** | **x** | **x** | **x** | **x** | **X** | **x** | **x** | **x** |
| Global Assessment of Functioning |  | **x** | **x** | **x** | **x** | **x** | **x** | **x** | **x** | **x** | **x** | **x** |
| Positive and Negative Symptom Scale |  | **x** | **x** | **x** | **x** | **x** | **x** | **x** | **x** | **x** | **x** | **x** |
| Hamilton Rating Scale for Depression |  | **x** | **x** | **x** | **x** | **x** | **x** | **x** | **x** | **x** | **x** | **x** |
| Mini Mental State^6^ Examination |  | **x** | **x** | **x** | **x** | **x** | **x** | **x** | **x** | **x** | **x** | **x** |
| THINC-it ®^6^ |  | **x** | **x** | **x** | **x** | **x** | **x** | **x** | **x** | **x** | **x** | **x** |
| Northoff Catatonia Rating Scale (German version) |  | **x** | **x** |  |  |  |  |  | **x** | **x** | **x** | **x** |
| Q-LES-Q-18 |  | **x** | **x** |  |  |  |  |  | **x** | **x** | **x** | **x** |
| Self-Stigma of Mental Illness Scale – Short Form |  | **x** | **x** |  |  |  |  |  | **x** | **x** | **x** | **x** |
| Stigma-Stress-Scale |  | **x** | **x** |  |  |  |  |  | **x** | **x** | **x** | **x** |

ECT: Electroconvulsive Therapy; mECT: Maintenance Electroconvulsive Therapy; TAU: treatment as usual; THINC-it: THINC integrative tool; Q-LES-Q-18: Abbreviated Quality of Life Enjoyment and Satisfaction Questionnaire

*Stabilization: implementation of any major medication changes before the initiation of the ECT series

** The times indicated as weeks refer to the TAU group, however the respective mECT should be scheduled within the respective week. Visit 2 is regarded to take place in week 0, e.g. calendar week 20. For the patients receiving mECT, the first mECT should be scheduled in the next calendar week, e.g. calendar week 21, and the 3^rd^ mECT (Visit 2a) should take place in calendar week 3 after V2, e.g. calendar week 23. A calendar week is from Monday to Sunday. Two mECTs cannot be performed in the same calendar week

^1^ Sociodemographics: Age, sex, education, marital status, residence

^2^ Vital signs: height, weight

^3^ All baseline characteristics (including vital signs, medical history, prior medication, …) must be assessed **before** randomization. Randomization should be carried out only in subjects with improvement of 30% or more on the Brief Psychiatric Rating Scale (BPRS).

^4^ According to randomization

^5^ Treatment depending on patients’ choice

^6^ Mini-Mental State Examination (MMSE) and Thinc-it must be performed before mECT is administered.

# ABBREVIATIONS

AE Adverse Event

BPRS Brief Psychiatric Rating Scale

CRF Case Report Form

CTCAE Common Terminology Criteria for Adverse Events

CTFG Clinical Trial Facilitation Group

CV Curriculum Vitae

DBL Data Base Lock

DMP Data Management Plan

DSMB Data Safety Monitoring Board

DVP Data Validation Plan

eCRF electronic Case Report Form

ECT Electroconvulsive Therapy

EU European Union

FAS Full Analysis Set

FSI First Subject In

GAF Global Assessment of Functioning

GCP Good Clinical Practice

GDPR General Data Protection Regulation

HAMD Hamilton Rating Scale for Depression

IC Informed Consent

ICH International Council on Harmonization of Technical Requirements for Registration of Pharmaceuticals for Human Use

ICH GCP ICH harmonized tripartite guideline on GCP

IEC Independent Ethics Committee

IIT Investigator-Initiated Trial

ISF Investigator Site File

ISRCTN International Standard Randomized Controlled Trial Number

KKS Coordination Centre for Clinical Trials (Koordinierungszentrum für Klinische Studien)

LDR Legally Designated Representative

LSLV Last Subject Last Visit

mECT Maintenance Electroconvulsive Therapy

MMSE Mini Mental State Examination

NCRS Northoff Catatonia Rating Scale

PANSS Positive and Negative Symptom Scale

PD Protocol Deviation

PI Principal Investigator

Q Quarter (time span)

Q-LES-Q-18 Abbreviated Quality of Life Enjoyment and Satisfaction Questionnaire

REDCap Research Electronic Data Capture

RDE Remote Data Entry

SC Steering Committee

SOP Standard Operating Procedure

SSMIS-SF Self-Stigma of Mental Illness Scale – Short Form

TAU Treatment as usual

TMF Trial Master File

# Introduction and Rationale

## Scientific Background

Schizophrenia is one of the most severe and costly mental disorders in terms of human suffering and societal expenditure (1-5). Life-time prevalence of schizophrenia is about 0.5–1.0%. Sustained recovery occurs in less than 14% within the first five years following a psychotic episode. Longer-term outcomes may be marginally better: a large international 25-year follow-up study reported an additional 16% with late-phase recovery. Throughout Europe, less than 20% of people with schizophrenia are employed (6). Years of potential life lost typically range between 10-20 years (7).

One major problem is that a significant proportion of patients - about 15-30 % - do not respond to all known antipsychotics, including clozapine, which is currently considered the gold-standard for treatment-resistant schizophrenia (8). These patients are among the most debilitated patients with a poor outcome prognosis in terms of medical and social rehabilitation. For these severely ill patients with persistent positive symptoms there are no further evidence-based alternatives or augmentation strategies. Hence, recent Cochrane database reviews stated (9, 10) that the quality of extant studies is too poor to recommend any intervention additional to clozapine and that new, properly conducted, randomized controlled trials independent from the pharmaceutical industry need to be performed to help these most severely impaired patients (9, 10).

Although ECT was initially used to treat schizophrenia and is recommended in national treatment

guidelines and by our national psychiatric associations (11, 12), it is nowadays by far underused in the therapy of schizophrenia in many countries, including Germany. This may be due to its stigma, but it is also a consequence of the development of antipsychotic medication, which however possesses its own inherent limitations and disadvantages. ECT is well known to be effective in treatment resistant schizophrenia and CRS (see e.g. (13-18)), and synergistic effects of clozapine and ECT have been demonstrated (19-23). However, relapse rates after successful courses of ECT are very high (16), and evidence for the use of maintenance ECT (mECT) in treatment resistant schizophrenia (24) or CRS (25) is scarce at best. At present, there are only case reports and a limited number of retrospective studies demonstrating that the clinical severity of the illness and re-hospitalizations can be significantly reduced with mECT (15, 25, 26).

## Study Rationale / Justification

In this multi-center trial, we aim to examine the effectiveness of mECT in treatment-resistant subjects with schizophrenia who improved after a course of routine ECT. If mECT will lead to a longer time to relapse and/or to a higher proportion of relapse-free subjects compared to those undergoing treatment as usual, this trial would have an enormous impact on therapeutic strategies for "treatment-resistant" subjects and would induce a profound change of current treatment guidelines, where ECT still ranks at the level of ultima ratio, despite accumulating evidence suggesting otherwise.

## Risk Benefit Assessment

All procedures performed during this study are routine clinical procedures and are mentioned within German guidelines. Of course, all side effects will be recorded. Severe side effects are not expected (27), since they are known to be extremely rare (and not study related).

The most common side effect in phase one will be cognitive side effects due to ECT. These will be monitored not only by MMSE, but also by THINC-it and by clinical observation. THINC-it has been validated multiple times in the past (28), especially for treatment-related changes of cognitive function in both depression (29) and schizophrenia (30). Of course, this monitoring will continue in phase two as well, although significant differences between groups are not expected to occur during this phase. Typically, cognitive side effects after an acute ECT series subside after about 15 days (31). There is no evidence for further decline of cognitive function with maintenance ECT (32), but evidence of further improvement.

Participants might personally benefit from study participation due to closer and more standardized monitoring compared to routine clinical practice. Future patients with clozapine-resistant schizophrenia will benefit from the study results, as they will most likely lead to a change in guidelines for treatment-resistant schizophrenia.

# Study Objectives and Endpoints

## Primary Objective and Primary Endpoint

The main purpose of the study is to show superiority of maintenance electroconvulsive therapy (mECT) plus treatment as usual (TAU) versus TAU only.

The primary endpoint is the time to relapse for which relapse is defined as Brief Psychiatric Rating Scale (BPRS) ≥20% higher than individual BPRS at start of phase II at any following study visit or any unscheduled readmission due to a worsening of psychiatric symptoms or any unscheduled visit with an BPRS ≥20% higher than individual BPRS at start of phase II.

The BPRS is evaluated by an unblinded rater at the site and a blinded central rater. Hospital readmission is decided by unblinded non-study related staff. The first relapse decision is used for analysis.

If the condition of a patient is worsening (assessed by unblinded staff), the BPRS assessment is videotaped for the evaluation by the blinded rater.

The time to relapse is the most important outcome parameter, when the effectiveness of interventions in subjects with schizophrenia is investigated. The BPRS is a widely used instrument in psychiatry for the assessment of psychotic symptoms and has been implemented in previous clinical trials and large-scale investigations (33). The instrument has been internationally validated and proven to be sensitive to change.

## Secondary Objectives and Endpoints

The secondary objectives are to compare side effect profile and safety as well as psychopathological changes between mECT plus TAU versus TAU only.

The secondary endpoint for treatment efficacy is the proportion of relapse free subjects at the end of phase II.

Further secondary endpoints are:

- BPRS
- Global assessment of functioning (GAF) allowing a general (34) and PANSS allowing a differentiated view on specific symptom dimensions (35)
- HAMD (36) monitoring depression, since ECT and mECT have a well-known positive influence on mood
- The Northoff catatonia rating scale (NCRS-dv) (37) assessing the full spectrum of catatonic symptoms
- Q-LES-Q-18, an abbreviated and validated Quality of Life Enjoyment and Satisfaction Questionnaire for subjects with schizophrenia (38)
- The Self-Stigma of Mental Illness Scale – Short Form (SSMIS-SF) (39) and the Stigma-Stress-Skala (40) are used for self-labeling and stigma
- MMSE (41) and THINC-it (28-30) monitoring cognition

All secondary endpoints listed above are analyzed at the end of phase II and at the end of follow-up.

Safety will be also determined by the frequency of adverse events from randomization up to the last follow-up visit.

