**Follow-Up period**

- Study visits 4a and b with psychometric assessments
- Treatment with or without mECT depending on patient’s choice regardless of randomization

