# Adverse Events

## Definitions

- - 1. Adverse Event

Following GCP, the definition of an adverse event (AE) is adapted as follows: Any untoward medical occurrence in a subject participating in a study and which does not necessarily have a causal relatedness with the study intervention. An AE can therefore be any unfavorable and unintended sign, symptom, or disease temporally associated with the study intervention, whether or not related to the study intervention.

An AE may be:

- New symptoms / medical conditions,
- New diagnosis,
- Intercurrent diseases and accidents,
- Worsening of medical conditions/ diseases existing before study start,
- Recurrence of disease,
- Increase of frequency or intensity of episodic diseases.

A pre-existing disease or symptom will not be considered an adverse event unless there will be an untoward change in its intensity, frequency or quality. This change will be documented by an investigator.

Surgical procedures themselves are not AEs; they are therapeutic measures for conditions that require surgery. The condition for which the surgery is required may be an AE. Planned surgical measures permitted by the study protocol and the condition(s) leading to these measures are not AEs, if the condition leading to the measure was present prior to inclusion into the study. In the latter case the condition should be reported as medical history.

AEs are classified as "non-serious" or "serious".

- - 1. Serious Adverse Event

Serious adverse event (SAE) is untoward medical occurrence that:

- Results in death,
- Is life-threatening (the term life-threatening refers to an event in which the subject was at risk of death at the time of event and not to an event which hypothetically might have caused death if it was more severe),
- Requires hospitalization or prolongation of existing hospitalization,
- Results in persistent or significant disability / incapacity*,
- Is a congenital anomaly / birth defect,
- Is otherwise medically relevant.

* Persistent or significant disability or incapacity means that there is a substantial disruption of a person's ability to carry out normal life functions. The irreversible injury of an organ function (e.g. paresis, diabetes, cardiac arrhythmia) fulfils this criterion.

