## Period of Observation and Documentation

Adverse events (AEs) will be ascertained by the investigators using non-leading questions, noted as spontaneously reported by the subjects to the medical staff at any time during the study or observed at any of the study visit.

The observation period begins with randomization and ends with the last study visit.

AEs with a grading ≥ 2 will be documented in the subject file and in the CRF. AEs of grade 1 will not be documented in the subject file and in the CRF. If applicable, all medical diagnoses or symptoms occurring prior to the beginning of the period of observation and documentation will be recorded in the CRF as medical history.

The following general rules apply to the documentation of the AEs and SAEs: The start date of an SAE must not be earlier than that of the corresponding AE. The end date of a SAE is typically the same as that of AE. The end date of the SAE must not be later than the end date of the corresponding AE. AEs and SAEs that are ongoing at the time of death are considered not resolved or resolving.

All SAEs and their relevance for the benefit-risk assessment of the study will be evaluated continuously during the study and for the final report. All SAEs will be documented in the CRF.

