## Secondary Analyses

The number of relapse free subjects at the end of phase II will be analyzed by a mixed logistic regression model (two-sided alpha=0.05) with planned treatment, strata and BPRS at baseline as fixed effects and site as random effect in all subjects randomized (ITT).

BPRS, GAF, PANSS, HAMD, NCRS-dv, Q-LES-Q-18, SSMIS-SF and stigma-stress-scale will be categorized considering relapses and dropouts as additional categories. These will be tabulated using standard descriptive measures including number of non-missing values, mean, standard deviation, extrema and quartiles.

Furthermore, to analyze BPRS, GAF, PANSS, HAMD, NCRS-dv, Q-LES-Q-18, SSMIS-SF and stigma-stress-scale per time-point linear mixed models with the respective scale at baseline, strata and treatment as fixed effects and site as random effect will be used.

An explorative analysis will be carried out for all recruited subjects, where a logistic regression will be performed for the rate of inclusion in the randomized trial on baseline criteria. This way, subjects likely to profit from a first session of ECT can be determined based on clinical criteria.

**Safety analysis:** Frequencies of subjects experiencing at least one adverse event (AE) will be displayed according to MedDRA terminology. MMSE and THINC-it will be analyzed by group using standard descriptive measures.

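### The adverse event endpoint pools 28 randomised weeks with 12 months of patient-chosen treatment and counts relapse as an adverse event, so the crude comparison is diluted and can favour mECT

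*Protocol*

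**What the plan says.** **Objective.** Section 2.2: "The secondary objectives are to compare side effect profile and safety as well as psychopathological changes between mECT plus TAU versus TAU only".

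**Window.** The same section fixes the AE endpoint: "Safety will be also determined by the frequency of adverse events from randomization up to the last follow-up visit". Section 8.3 agrees: "The observation period begins with randomization and ends with the last study visit". Section 3.3 gives phase II 28 weeks and follow-up 12 months. During follow-up (section 6), treatment with or without mECT is the patient's "choice regardless of randomization". Section 9.4 censors relapse-free patients at visit 3 because the intervention may change from then on.

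**What counts as an AE.** Section 8.1.1 lists "Worsening of medical conditions/ diseases existing before study start" and "Recurrence of disease". Section 8.1.2 makes an event serious if it requires hospitalisation. The one exemption is admission without an underlying AE. Section 8.3 documents events of grade 2 or higher only.

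**Output.** Section 9.5: "Frequencies of subjects experiencing at least one adverse event (AE) will be displayed according to MedDRA terminology".

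**Phase I.** Section 1.3, which also covers side effects in phase I, says: "Of course, all side effects will be recorded".

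**The concern.** The safety objective is a contrast between mECT plus TAU and TAU alone. That contrast is randomised from visit 2 and is protected only until visit 3. Counting AEs to the end of follow-up adds a year in which control patients may take up mECT and mECT patients may stop it. A real difference in harm is then diluted.

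Relapse is the primary efficacy event, and by definition it is also an AE. If mECT prevents relapse, the share of patients with at least one AE falls in that arm for that reason alone. A summary meant to show the price of mECT would partly restate its benefit.

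**Working it through.** **1. Planning figures (section 9.9).** Relapse 85% (TAU) and 45% (mECT + TAU); missing 15% and 30%.
- Composite rate = m + (1 − m)p: 0.15 + 0.85 × 0.85 = 0.8725; 0.30 + 0.70 × 0.45 = 0.615.
- Hazard = −ln(1 − rate)/6 months: 0.3433 and 0.1591; ratio 0.4634. All match the protocol.
- Expected events 42 × (0.8725 + 0.615) = 62.5. The Schoenfeld formula gives power 0.860 (stated 0.85), and 0.800 at an mECT hazard of 0.17 (stated about 0.80).

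The inputs are sound. The protocol gives no figure for the AE comparison itself.

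**2. Share of the window on patient-chosen treatment.** 28 weeks / 4.345 = 6.44 months. 12 / (6.44 + 12) = 0.65. This is the planned share for a patient followed to the last visit.

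**3. Relapse AEs per 42 subjects.**

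| | TAU | mECT + TAU |
| --- | --- | --- |
| No missing data | 42 × 0.85 = 35.7 | 42 × 0.45 = 18.9 |
| Missing subjects excluded | 42 × 0.85 × 0.85 = 30.3 | 42 × 0.70 × 0.45 = 13.2 |

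Both rows assume that every relapse is grade 2 or higher. The gap is about 17 subjects either way.

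**4. Effect on the any-AE percentage.** Assumptions, not in the protocol: other AEs are independent of relapse; a share b of TAU subjects (20% to 40%) has another AE; the mECT share is b + r, where r is the true excess. Any-AE = 1 − (1 − relapse)(1 − other), using the first row above.

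| | b = 20% | b = 40% |
| --- | --- | --- |
| TAU | 1 − 0.15 × 0.80 = 88% | 1 − 0.15 × 0.60 = 91% |
| mECT, r = 0 | 1 − 0.55 × 0.80 = 56% | 1 − 0.55 × 0.60 = 67% |
| mECT, r = 20 points | 1 − 0.55 × 0.60 = 67% | 1 − 0.55 × 0.40 = 78% |

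The arms break even at r = (1 − b)(1 − 0.15/0.55), which is 58 points at b = 20% and 44 points at b = 40%. Below that, the crude figure favours mECT.

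**5. Effect of the long window.** Assumptions, not in the protocol: AE rates of 0.05 per month on mECT and 0.02 off it; the same share of both arms on mECT in follow-up. The phase II rate ratio is 0.05/0.02 = 2.5. Over the whole window:
- No follow-up mECT: (0.05 × 6.44 + 0.02 × 12)/(0.02 × 6.44 + 0.02 × 12) = 1.52.
- Half on mECT (follow-up rate 0.035): (0.05 × 6.44 + 0.035 × 12)/(0.02 × 6.44 + 0.035 × 12) = 1.35.

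**The case against.** The strongest reply is that the data needed are all collected. AEs are shown by MedDRA term, so relapse and other harms should appear on different lines. Start dates, seriousness and relatedness are recorded (sections 6.2 and 8.2.2), and MMSE and THINC-it are analysed by group, including at the end of phase II. AE tables by period, or without relapse terms, are ordinary SAP content. Section 9.5 does not even say that AEs are compared by randomised arm; that is inferred from the objective in 2.2 and the intention-to-treat text in 9.1. This reply stands against any claim that the safety question is unanswerable. It does not remove the point, because the protocol itself fixes the window and the AE definition and names the any-AE frequency as the output.

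A reader might infer more, in four ways that the protocol does not support.
- **Starting at randomisation spoils the comparison.** It does not. Both arms have completed acute ECT by then, so phase I events carry no information on mECT plus TAU versus TAU.
- **Every primary event is an AE or SAE.** Section 9.4 counts missing information as relapse, and a dropout is not an AE. Grade 1 events are not recorded, and a 20% BPRS rise has no assigned grade. Only readmissions meet the hospitalisation criterion.
- **Unequal observation time makes mECT look safer.** This arises only if AE observation stops at relapse. No section says so plainly; 7.2 ends the study intervention. Stopping there would give a mean of 0.8725/0.3433 = 2.54 months under TAU and 0.615/0.1591 = 3.87 under mECT. The longer time would raise the mECT count, which is the opposite direction. It also conflicts with the 65% share, which presumes continued follow-up.
- **The DSMB sees nothing from acute ECT.** Section 12.5 does not list what the DSMB receives. MMSE and THINC-it are scheduled at visits 1 and 2, and 8.3 allows earlier symptoms to be entered as medical history.

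**Conclusion.** The concern holds in a limited form: the AE comparison is poorly specified, not impossible. About 65% of its planned window is not randomised treatment, although the primary analysis stops at visit 3 for that very reason. The any-AE frequency also carries the efficacy event. Up to about 36 versus 19 subjects per 42 would have a relapse AE, or 30 versus 13 with missing subjects excluded. These counts rest on the section 9.9 rates and on every relapse being grade 2 or higher. The any-AE percentages and the rate ratios of 1.35 to 1.52 also rest on assumed AE rates and follow-up uptake, and they illustrate direction only.

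Sections 1.3 and 8.3 contradict each other, which is a separate matter with no bearing on the arm comparison. The first says all side effects are recorded. The second starts at randomisation and omits grade 1. As written, no AE record is required during phase I ECT, and none for the 140 − 84 = 56 or so enrolled subjects who are not randomised.

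**What to change.** In sections 2.2 and 9.5:
- Make randomisation to visit 3 the main between-arm AE and SAE comparison, and state that it is by randomised arm.
- Tabulate AEs that are primary-endpoint events (relapse, psychiatric readmission) separately, and show the main table without them. They are still collected and reported as now.
- Add exposure-adjusted rates as a supplement.
- Present follow-up AEs descriptively, by treatment received.

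This costs a little programming and a shorter main safety window. It needs no new data or visits.

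Separately, bring 1.3 and 8.3 into line. Either 1.3 states the limits that 8.3 sets, which is a text change only, or 8.3 extends recording into phase I, which adds eCRF entries over at most 6 weeks and no visits.
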